# Ursodeoxycholic acid versus placebo in the treatment of women with intrahepatic cholestasis of pregnancy (ICP) to improve perinatal outcomes: protocol for a randomised controlled trial (PITCHES)

**DOI:** 10.1186/s13063-018-3018-4

**Published:** 2018-11-27

**Keywords:** Cholestasis, Pregnancy, Ursodeoxycholic acid, Perinatal, Stillbirth

## Abstract

**Background:**

Intrahepatic cholestasis of pregnancy (ICP) is the most common liver disorder specific to pregnancy and presents with maternal pruritus, raised concentrations of serum bile acids and abnormal liver function tests. ICP is associated with increased rates of spontaneous and iatrogenic preterm labour, fetal hypoxia, meconium-stained amniotic fluid and intrauterine death. Some clinicians treat ICP with ursodeoxycholic acid (UDCA) to improve maternal pruritus and biochemical abnormalities. However, there are currently no data to support the use of UDCA to improve pregnancy outcome as none of the trials performed to date have been powered to address this question.

**Methods:**

The PITCHES trial is a triple-masked, placebo-controlled randomised trial, to evaluate UDCA versus placebo in women with ICP between 20 + 0 to 40 + 6 weeks’ gestation. The primary objective of the trial is to determine if UDCA treatment of women with ICP between 20 + 0 and 40 + 6 weeks’ gestation reduces the primary perinatal outcome: a composite of perinatal death (as defined by in utero fetal death after randomisation or known neonatal death up to 7 days) or preterm delivery (less than 37 weeks’ gestation) or neonatal unit admission for at least 4 h (from infant delivery until hospital discharge). The secondary objectives of the trial are (1) to investigate the effect of UDCA on other short-term outcomes for both mother and infant and (2) to assess the impact of UDCA on health care resource use, in terms of the total number of nights for mother and infant, together with level of care.

**Discussion:**

Current practice in the UK at the time of trial commencement for the treatment of ICP is inconsistent, with some units routinely prescribing UDCA, others prescribing very little and the remainder offering it variably. Our previous pilot trial of UDCA in women with ICP demonstrated that the trial would be feasible, and the research question remains active and unanswered. Results are highly likely to influence clinical practice, through direct management and impact on national and international guidelines.

**Trial registration:**

ISRCTN registry, ID: ISRCTN91918806. Prospectively registered on 27 August 2015.

**Electronic supplementary material:**

The online version of this article (10.1186/s13063-018-3018-4) contains supplementary material, which is available to authorized users.

## Background

Intrahepatic cholestasis of pregnancy (ICP), also called obstetric cholestasis, is the most common liver disorder specific to pregnancy. It presents with maternal pruritus, raised concentrations of serum bile acids and abnormal liver function tests. The maternal symptoms typically resolve postpartum, but affected women have an increased risk of hepatobiliary disease in later life [1]. ICP is associated with increased rates of spontaneous and iatrogenic preterm labour, fetal hypoxia and meconium-stained amniotic fluid [2–4]. There are also reports of increased rates of intrauterine death [5–7], although the incidence is low [4, 8]. Some clinicians treat ICP with ursodeoxycholic acid (UDCA) [9, 10] to improve maternal pruritus and biochemical abnormalities. However, there are currently no data to support the use of UDCA to improve pregnancy outcome as none of the trials performed to date have been powered to address this question.

UDCA is a naturally occurring bile acid that is present in small amounts in humans. It is relatively hydrophilic and has several actions that result in improvement of cholestasis. It increases biliary bile-acid excretion by post-translational modification of hepatic bile-acid transporters, enhances renal bile-acid excretion and has anti-apoptotic effects [11]. UDCA improves outcomes in primary biliary cirrhosis in addition to maternal symptoms in ICP [12]. Adverse events are only infrequently reported in pregnancy [13]; some women experience gastrointestinal side-effects (such as diarrhoea), but in the largest trial to date there were no significant differences in the incidence of reported side-effects in UDCA and placebo groups [2]. Other therapeutic options in ICP include rifampicin, cholestyramine, *S*-adenosyl methionine, guar gum and dexamethasone, but the small studies of these drugs in women with ICP have not consistently shown that they improve maternal symptoms or serum bile-acid concentrations [3].

The main clinical research question is whether adverse pregnancy outcomes can be reduced in women with ICP by treatment with UDCA. This is a subject of intense debate. The current UK guideline (from the Royal College of Obstetricians and Gynaecologists) on the management of ICP describes the evidence relating to the use of UDCA and states that ‘UDCA improves pruritus and liver function in women with obstetric cholestasis’ but ‘women should be informed of the lack of robust data concerning protection against stillbirth and safety to the fetus or neonate’. The guideline concludes that: ‘as the pathophysiology of obstetric cholestasis and the mechanism of fetal demise are uncertain, the possible role of UDCA is unclear. Further larger studies are required to determine this’. The latest updated Cochrane review [13] judged many of the trials of UDCA in ICP to be at moderate to high risk of bias. Trials to date have lacked power to demonstrate whether UDCA is fetoprotective, with numbers of participants and adverse events too small to enable the recommendation of UDCA. The Cochrane review concluded that larger trials of UDCA to determine fetal benefits or risks are needed.

If UDCA is found to be beneficial in ameliorating adverse perinatal outcomes, once published these results would be highly likely to lead to an immediate change in clinical practice, through individual choice of clinicians and women, and through changing national/international guidelines.

The PITCHES trial is a triple-masked, placebo-controlled randomised trial to evaluate UDCA versus placebo in women with ICP between 20^+ 0^ to 40^+ 6^ weeks’ gestation. The primary objective of the trial is to determine if UDCA treatment of women with ICP between 20^+ 0^ and 40^+ 6^ weeks’ gestation reduces adverse perinatal outcomes up to infant hospital discharge. The secondary objectives of the trial are (1) to investigate the effect of UDCA on other short-term outcomes for both mother and infant and (2) to assess the impact of UDCA on health care resource use, in terms of the total number of nights for mother and infant, together with level of care.

## Methods

### Study setting

The study will be conducted in approximately 30 consultant-led maternity units in England and Wales. A list of participating study sites is available on the study website: www.npeu.ox.ac.uk/pitches.

### Inclusion criteria

Women will be considered eligible for inclusion into the trial if they fit the following criteria:ICP (pruritus with a raised serum bile acid above the upper limit of normal for the local laboratory)20^+ 0^ to 40^+ 6^ weeks’ gestation on day of randomisation (see note below on gestational age)No known lethal fetal anomalySingleton or twin pregnancyAged 18 years or overAble to give written informed consent

### Exclusion criteria

Women will be excluded from the trial if:A decision has already made for delivery within the next 48 hThere is a known allergy to any component of the UDCA or placebo tabletsthere is a triplet or higher-order multiple pregnancy

### Intervention

The Investigational Medicine Product (IMP) is ursodeoxycholic acid (UDCA) or matching placebo, manufactured and supplied by [name], GmBH. The most recent Summary of Product Characteristics for UDCA can be found at http://www.medicines.org.uk/emc/medicine/27444. Possible side-effects include gastrointestinal disorders (reported as common, i.e. ≥ 1/100 to < 1/10 patients) or skin and subcutaneous disorders (reported as very rare, i.e. < 1/10,000 patients), as listed in the Summary of Product Characteristics.

#### Formulation and packaging

In the treatment arm, each film-coated tablet contains the active ingredient: 500 mg UDCA and the inactive ingredients of magnesium stearate, polysorbate 80, providone K 25, microcrystalline cellulose, colloidal anhydrous silica, crospovidone and talc. In the control arm, a matching placebo tablet, identical in colour and shape to the treatment arm contains the inactive ingredients: magnesium stearate, polysorbate 80, providone K 25, microcrystalline cellulose, colloidal anhydrous silica, crospovidone and talc. The coating ingredients for both are talc, hypromellose and macrogol 6000. The IMP will be packaged into high-density polyethylene bottles, with 32 tablets per bottle, and will be administered orally. The IMP does not require any special storage conditions.

#### Dosing

The starting dose will be 1000 mg daily (500 mg twice a day), increased in increments of 500 mg per day every 3–14 days if there is no biochemical or clinical improvement, based on clinical decision, to a maximum of 2000 mg per day. The dose of IMP may be reduced to 500 mg daily. Divided doses will be spread evenly throughout the day. There is no need to take it with or without food and this will be left to participant preference. The IMP will be continued until delivery. The duration of treatment will range from 1 day to a maximum of 22 weeks, for a participant randomised at 20 weeks’ gestation who does not deliver until 42 weeks. At each antenatal follow-up visit with a member of the research team, women will be asked the percentage of IMP that they have taken since their last appointment and this will be recorded.

### Study procedures

#### Recruitment, eligibility and consent

Members of the research team will provide a full verbal explanation and written description of the trial to women who meet the inclusion criteria (as above). The woman will be given sufficient time to consider the information, and to decide whether she will participate in the trial. Written informed consent will be sought from the woman and taken by an appropriately trained physician. Baseline data, including all demography, serum bile-acid concentrations and liver function tests, together with an itch visual analogue score (worst itch in the previous 24 h) completed by the woman will be entered on a web-based database by members of the research team at the time of study enrolment. On completion of these details, the database will issue a pack number to the local hospital pharmacy for dispensing.

Participants will be reviewed at routine care clinic visits until delivery. Serum bile acids and liver function tests will be monitored according to usual clinical practice. The woman will be asked for a value of the worst itch she felt during the previous 24 h. The Investigational Medicinal Product (IMP) dose will be altered at the discretion of the responsible clinician. If maximal doses of the IMP have been reached, consideration can be given to the addition of other therapy, e.g. rifampicin, in addition to the trial therapy, without breaking the allocation code. The remainder of antenatal care, in particular the timing and mode of delivery will be left to the discretion of the responsible clinician. A schedule of participant enrolment, interventions and assessments in the trial is shown in Fig. 1.

**Fig. 1 Fig1:**
[figure not shown]
Schedule of participant enrolment, interventions and assessments in the trial. 1. All screening assessments are part of routine clinical practice. 2. Weekly visits are recommended but not mandatory; normal hospital clinical practice is acceptable. 3. No other trial-specific procedures are required before consent. 4. These blood tests are taken as per routine clinical practice and are not trial specific. 5. Investigational Medicinal Product (IMP) started after randomisation. IMP dose altered by the research team if indicated by symptoms and/or blood tests taken during normal clinical practice. 6. Cardiotocography only measured 1 week after randomisation or as per routine clinical practice. 7. All unexpected adverse events occurring during the trial that are observed by the research team or reported by the participant will be recorded in the electronic Case Report Form, whether or not attributed to the IMP. Unexpected serious adverse events will be expeditiously reported. 8. All prescribed medications deemed necessary by the investigator to provide adequate supportive care for ICP are permitted during the clinical trial. The medications must be recorded in the participant’s electronic Case Report Form; all other concomitant medication will only be recorded in the event that a serious adverse event is reported

A woman will be free to withdraw from the clinical trial at any time without the need to provide any reason or explanation; and that this decision will not impact on any aspect of her ongoing clinical care. Women who withdraw will be asked if they are willing for their outcomes to be collected by case note review. If there is sufficient time within the existing study time-line, additional participants will be recruited up to the number of women who discontinued the intervention or withdrew.

Outcomes will be recorded on the web-based database through case note review by trained researchers after discharge of the mother and baby.

The end of the trial will be defined as the date when the trial database is locked. An end-of-trial declaration will be made to the Medicines and Healthcare products Regulatory Agency and the approving Research Ethics Committee.

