### Assessment of safety and reporting

At each clinic visit, a member of the clinical or research team will ask the woman if she has had any adverse events, and will ensure that she has appropriate clinical monitoring as routinely performed in each maternity unit. Standard definitions of an adverse event, adverse reaction, serious adverse event, serious adverse reaction and suspected unexpected serious adverse reaction will be followed. The relationship of each adverse event to the IMP will be determined by a medically qualified individual according to the usual definitions of causality. The period for safety reporting will be from first dose of IMP until discharge of mother and discharge of infant. Expectedness will be determined according to the Summary of Product Characteristics for UDCA. Standard reporting guidelines will be followed.

The following expected adverse events and serious adverse events are considered to be expected in this population of pregnant women or a result of the routine care/treatment of a participant and as such do not need to be recorded:Worsening pruritusAdmission in active labourAdmission for cervical ripening or induction of labourAdmission for caesarean sectionAdmission for assessment for suspected fetal compromise, including poor growth, or reduced fetal movementsAdmission for monitoring for hypertension, antepartum haemorrhage, suspected preterm labour, pre-labour rupture of the membranes or other reasons for monitoringAdmission for psychiatric or social reasonsAdmission for unstable lie or external cephalic version.

The following fetal and neonatal outcomes are pre-specified outcomes and as such will be recorded on electronic Case Record Forms but not expeditiously reported:Neonatal unit admissionStillbirth and perinatal death (within 7 days)Preterm delivery (< 37 completed weeks’ gestation)Meconium staining of the amniotic fluid or placentaSmall for gestational ageSeizuresEncephalopathy (treated with hypothermia)Need for respiratory support – ventilation via an endotracheal tube (ETT) or nasal continuous positive airway pressure (CPAP)Sepsis requiring antibiotics with symptoms or confirmed blood or cerebrospinal fluid (CSF) culture

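### The protocol uses two conflicting senses of expected for adverse event recording; under one of them, UDCA's labelled gastrointestinal reactions need not be recorded

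*Protocol article*

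**What the plan says.** Four places in the protocol article bear on which adverse events are recorded.

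- **Fig. 1, note 7** (Study procedures): "All unexpected adverse events occurring during the trial that are observed by the research team or reported by the participant will be recorded". The sentence ends by saying that these events "will be recorded in the electronic Case Report Form, whether or not attributed to the IMP". A separate sentence then covers expedited reporting of unexpected serious events.
- **Assessment of safety and reporting, first paragraph:** at each clinic visit "a member of the clinical or research team will ask the woman if she has had any adverse events"; a medically qualified person judges causality for each event; and "Expectedness will be determined according to the Summary of Product Characteristics for UDCA".
- **Assessment of safety and reporting, lists:** eight items are exempt from recording because they are expected in pregnancy or arise from routine care. They are worsening pruritus and seven kinds of admission. The closing paragraph defines an unexpected serious adverse event as a serious event that is missing from the protocol's own list.
- **Intervention:** "Possible side-effects include gastrointestinal disorders (reported as common, i.e. ≥ 1/100 to < 1/10 patients"), and skin and subcutaneous disorders are given as very rare (below 1 in 10,000). Both are attributed to the product label.

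The Outcomes section, including its descriptive maternal and perinatal lists, has no gastrointestinal or tolerability item.

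**The concern.** Expectedness normally decides how fast an event is reported, not whether it enters the database. Note 7 makes it a condition of recording, and the only general standard of expectedness that the article states is the drug label. A site that follows those two sentences literally could leave out the reactions already known for the drug.

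What is at stake is the between-arm comparison of tolerability. The Background names diarrhoea as a known effect and reports that the largest previous trial found no significant difference in side-effects between UDCA and placebo. Under the label-based reading this trial could not re-examine that finding. Because note 7 applies whatever the attribution, gastrointestinal events would be missing from the placebo arm as well, so the background rate would be lost too.

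**Working it through.** **1. The two readings side by side**

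| | Label-based reading | List-based reading |
|---|---|---|
| Meaning of unexpected in note 7 | Not in the UDCA product label | Not on the protocol's exempt list |
| Textual support | The expectedness sentence in the safety section | The exempt list, and the closing definition of an unexpected serious event |
| Non-serious diarrhoea | Expected, so need not be recorded | Unexpected, so recorded |
| Skin reaction named in the label | Expected, so need not be recorded | Unexpected, so recorded |

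**2. Does note 7 settle it?** No. Expedited reporting has its own sentence, so in the first sentence the word unexpected does limit recording. But the second sentence uses the same word for serious events, and the safety section defines that term by the list. The list-based definition is given for serious events only, and diarrhoea would usually be non-serious.

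**3. Could the events be recovered elsewhere?** Not from what is listed. The descriptive maternal outcomes include the maximum dose of trial medication but no side-effects. Note 8 to Fig. 1 has medication other than that for ICP recorded only when a serious adverse event is reported, so treatment given for diarrhoea would not reveal the event.

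**4. Number of women.** The Sample size section's figure reproduces. For 40% against 27%, two-sided 5%, 90% power, pooled variance without continuity correction, mean p = 0.335:

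n = [1.960 × √(2 × 0.335 × 0.665) + 1.282 × √(0.40 × 0.60 + 0.27 × 0.73)]² / 0.13² = 275 per group

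275 / 0.95 = 289.5, so 290 per group. That calculation counts infants, but the same section sets recruitment at 580 women; with 1:1 allocation, 580 / 2 = 290 women per arm.

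**5. Events at stake on UDCA under the label-based reading**

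- Gastrointestinal, lower end: 290 × 0.01 = 2.9
- Gastrointestinal, upper bound (not reached): 290 × 0.10 = 29
- Skin, upper bound: 290 × 0.0001 = 0.03, so negligible in number

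**6. Would a comparison be informative?** The document gives no placebo rate, so these rates are assumptions for illustration. With 290 per arm, two-sided 5%:

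z = [|p₁ − p₀| × √290 − 1.960 × √(2p̄(1 − p̄))] / √(p₀(1 − p₀) + p₁(1 − p₁))

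For 1% against 5%: z = (0.04 × 17.03 − 1.960 × 0.2412) / 0.2396 = 0.87, power 81%. In the same way, 5% against 10% gives 63% and 5% against 15% gives 98%. If the data are kept, the trial could detect some plausible differences.

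**The case against.** The strongest reply is that the list-based reading is the more natural one. The safety section links expectedness to recording only through its exempt list, and no gastrointestinal or skin event is on it. The label sentence stands among regulatory reporting terms, so it may serve only to classify reactions for expedited reporting. Asking women about any adverse event, and judging causality for each, fits poorly with a rule that discards gastrointestinal events. The article also condenses a fuller protocol that is not shown and may settle the matter.

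Much of this stands. A reader might infer that the known side-effects are simply not captured. The documents do not support that: they support only that one stated rule permits it. Nor do they support the inference that the adverse event table would look falsely clean, since the article describes no such table.

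The reply does not remove the conflict. Asking is not recording, the article does not confine the label sentence to expedited reporting, and the list-based definition is written for serious events. This is not a detail left out for brevity; the stated rules give different answers for the same event.

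A reader might also stress a fourfold dose range. The ratio 2000 / 500 = 4 is right, but the lower figure is reached only by reduction ("The dose of IMP may be reduced to 500 mg daily"). Upward titration runs from 1000 to 2000 mg daily, a ratio of 2. The point does not rest on dose.

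**Conclusion.** The point holds as an unresolved contradiction about which adverse events are recorded. It does not hold as an established loss of data. If the label-based reading is followed, about 3 to 29 women on UDCA would have a gastrointestinal reaction that need not be recorded, and the arms could not be compared on the one side-effect that the label calls common. If the list-based reading is followed, nothing is lost. If sites differ, capture is inconsistent and observed frequencies in both arms are too low. Allocation is masked and minimised on centre, so there is no clear reason for this to favour one arm.

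The range assumes about 290 women receiving UDCA, and that the label frequency applies to this population at the doses used. The article does not tie that frequency to a dose.

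This should be fixed, but it is not critical: the sample size and the analyses of the listed outcomes are unaffected.

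**What to change.** Reconcile Fig. 1 note 7 with both parts of the safety section:

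- Reword note 7 so that all adverse events observed or reported are recorded in both arms, except those on the explicit exempt list.
- State that expectedness by the product label is used only to decide expedited reporting.
- Make clear that non-serious gastrointestinal and skin events are therefore recorded.
- Tabulate the recorded events by arm. Recording the dose at onset is an optional addition, not part of the correction.

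The cost is a change of wording and modest extra data entry for non-serious events; women are already asked at each visit. No dose or clinical rule changes. Trial status gives the end of recruitment as 31 August 2018, so for women already followed up the rewording cannot restore events that were not entered. For them, the trial report should say which recording rule the sites applied.
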